## **2.4 Methodology**

### **2.4.1 Trial design**

This is a multicenter, double-dummy, participant-blinded, randomized controlled clinical trial at 4 centers in China.

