#### **2.4.1.1 Randomization**

This study, we will use blocks randomization, stratified according to center. A central randomization system will be applied in our trial. The randomizing scheme will be produced by staff of the Research Center of Clinical Epidemiology affiliated to Peking University using statistical analysis software SAS9.4 with “proc plan” program. After production, it will be signed and sealed by the staff who produce it and keep by other staff who take no part in this trial. It will not be allowed to be checked by anyone except the top system administrator. Acupuncturists in each center will be responsible for getting random numbers. Via inputting the participants’ sex and birthday in the central randomization system through the phone or the web, they will get the random number.

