| VAS                                    | ×            |            | ×         | ×       | ×     | ×         | ×  | ×  |
| ≥ 50% migraine responder rate          | ×            |            | ×         | ×       | ×     | ×         | ×  | ×  |
| Intake of acute pain medication        | ×            |            | ×         | ×       | ×     | ×         | ×  | ×  |
| Assessment of blinding                 |              |            |           | ×(1.5C) | ×(3C) |           |    |    |
| Participant's compliance               |              |            | ×         | ×       | ×     |           |    |    |
| Adverse events                         | ×            | ×          | ×         | ×       | ×     | ×         | ×  | ×  |

MRM: menstrually related migraine; VAS: visual analogue scale.

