| 3   | Randomization   | The central randomization will be performed by the Research Center of Clinical Epidemiology affiliated to Peking University in China, which use block randomization to generate the random allocation sequence and prepare predetermined computer made randomization opaque sealed envelopes.                                                                                                                                                                                  | We randomly assigned each participant to acupuncture or medication groups via a central randomization system using a 1:1 ratio, which was performed by the Research Center of Clinical Epidemiology affiliated to Peking University. Randomization was stratified by centers with a fixed block size of 4.                                                                                                                                                                     |
| 4   | Primary outcome | a. The change of migraine days inside the menstrual cycle
b. The proportion of responders (defined as the proportion of patients with at least a 50% reduction of the number of menstrual migraine days).                                                                                                                                                                                                                                                                   | Change from baseline in average number of migraine days per perimenstrual period over cycles 1-3.                                                                                                                                                                                                                                                                                                                                                                              |

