#### **Statistical Comparisons Between Groups**

Continuous variables will be compared using a *t* test or Wilcoxon rank-sum test if data show serious deviations from a normal distribution. Categorical data or ordinal data will be compared using a Chi-square test or Fisher's exact test, as appropriate. All tests will be two-sided.

For the analysis of the primary and secondary outcomes, estimated treatment differences and associated 95% two-sided confidence intervals will be presented.

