#### **6.3.4 Analyses for Secondary Outcome**

Efficacy analyses for all secondary outcomes will be performed in the ITT population observed cases, with imputation of missing data using LOCF method.

The mixed-effect model (using baseline value as a covariate, treatment as a fixed effect, and center as a random effect) will also be used for secondary outcomes of the changes from baseline in average number of migraine days per outside perimenstrual period, mean migraine hours during perimenstrual period and outside perimenstrual period, mean pain visual analogue scale (VAS) during perimenstrual period and outside perimenstrual period. For proportion of participants with at least 50% reduction from baseline in number of migraine days and proportion of participants using acute pain medication will be compared between groups using a Chi-square test or Fisher's exact test, as appropriate.

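### Responder rate and acute-medication use are compared without centre or baseline; the tests are valid, but an adjusted risk difference would be more precise and would match the continuous outcomes

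*Supplement*

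**What the plan says.** Protocol 2.4.1 describes a "randomized controlled clinical trial at 4 centers in China". Protocol 2.4.1.1 says "we will use blocks randomization, stratified according to center", and the final-version column of the table in Protocol section 11 adds "Randomization was stratified by centers with a fixed block size of 4" and allocation "via a central randomization system using a 1:1 ratio".

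SAP 6.3.4 gives the listed continuous secondary outcomes a mixed-effect model with the baseline value as covariate and centre as a random effect. For the responder rate and acute-medication use it then says: "proportion of participants using acute pain medication will be compared between groups using a Chi-square test", with Fisher's exact test as the alternative. Neither centre nor a baseline covariate appears. Protocol 8.1 names the mixed-effect model, the t test, the rank-sum test, chi-square and Fisher together for the secondary outcomes, without assigning them one by one.

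SAP 6.3.1 promises, for primary and secondary outcomes alike, that "estimated treatment differences and associated 95% two-sided confidence intervals will be presented". It names no effect measure or interval method for a proportion.

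Baseline data exist. Women keep a headache diary for three baseline cycles (Protocol 2.4.2.4). The row "Intake of acute pain medication" is marked at baseline in the schedules of both the protocol (Figure 3) and the SAP (section 4). The diary also records the name, dose and time of each acute medicine (Protocol 2.4.4.1).

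**The concern.** The same section treats two kinds of secondary outcome differently and gives no reason. A covariate that predicts the outcome removes variance from the treatment comparison at no cost in patients, and here the covariates are already in the database. Acute-medication use is defined as any use in the period, so a woman's earlier use enters neither the endpoint nor the analysis.

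What is at stake is the width of the interval, and the chance of detecting a difference, for two secondary outcomes in each of two periods (cycles 1-3 and 4-6). The primary conclusion is not affected.

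**Working it through.** **The plan's own figure.** The plan gives no precision or power figure for the binary outcomes. Its only calculation is for migraine days: 3.1 (SD 2.7) against 5.2 (SD 4.4), two-sided 5%, 90% power, 68 per arm.

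- The normal formula gives (1.960 + 1.282)² × (2.7² + 4.4²) / 2.1² = 10.51 × 26.65 / 4.41 = 63.5, so 64 per arm.
- A t-based calculation gives 65. The rank-sum version, 65 × π/3, gives 68.1, which matches the stated 68.
- 68 / (1 − 0.20) = 85 per arm, against 86 planned (172 in total).

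Only the total of 172 is carried into the check below.

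**Precision as planned.** With 86 per arm and a rate near 50% (assumed), the unadjusted 95% half-width is 1.96 × √(2 × 0.25 / 86) = 14.9 percentage points.

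**What adjustment recovers.** The documents give no event rates, centre effects or baseline correlations, so these are assumptions.

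- Design: 172 women, four centres (44, 44, 44 and 40), 1:1 in blocks of 4, 3,000 runs per scenario.
- Effects: logit intercept −0.5 (a control rate of about 38% before centre and covariate spread) and a conditional log-odds ratio of 0.9.
- Centre SD (logit scale) and the baseline effect (logits per SD) were varied.
- Comparators: Pearson chi-square, Cochran-Mantel-Haenszel (CMH) stratified by centre, and logistic regression with treatment, centre and baseline. Variance change compares the standardised risk difference from that model with the crude one.

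| Centre SD | Baseline effect | Variance change | Power: chi-square | Power: CMH | Power: logistic |
|---|---|---|---|---|---|
| 0 | 0 | +0.5% | 84.3% | 84.3% | 83.6% |
| 0.3 | 0 | +0.8% | 82.2% | 82.2% | 81.9% |
| 0.6 | 0 | +0.7% | 79.2% | 80.0% | 80.3% |
| 0 | 0.5 | −4.3% | 80.7% | 80.6% | 81.1% |
| 0.3 | 0.5 | −5.9% | 80.1% | 80.1% | 81.5% |
| 0.3 | 1.0 | −16.8% | 68.9% | 68.9% | 76.0% |
| 0.6 | 1.5 | −26.6% | 55.7% | 55.9% | 68.7% |

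Monte Carlo error is about 0.7 to 0.9 points for power. Compare power only within a row: a fixed conditional odds ratio implies a smaller risk difference as the covariate strengthens (0.22 in the first row, 0.15 in the last).

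- **Centre alone** (first three rows): variance moves by less than 1%, with no gain, and power by about one point at most. The logistic model in these rows also carried a covariate with no effect, which accounts for any slight rise.
- **Baseline added:** variance falls by about 4 to 6% (weak), 17% (moderate) and 27% (strong).
- **Validity:** with no treatment effect (runs at an intercept of 0), chi-square rejected in 4.1 to 6.0% of runs (Monte Carlo error about 0.4 points). CMH gave much the same rate in each scenario. The unadjusted interval covered in 94 to 96% of runs.

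**On the interval scale.** A 5% reduction gives 14.9 × √0.95 ≈ 14.6 points; a 27% reduction gives 14.9 × √0.73 ≈ 12.8 points.

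**The case against.** The strongest reply is that nothing here is wrong. Chi-square and Fisher tests are legitimate in a randomised trial, the outcomes are secondary, and the gain depends on a correlation that the documents do not give. That stands as far as validity goes. It limits the point to an improvement but does not remove it, since the covariates are already collected and already used for the continuous outcomes.

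Four stronger readings are tempting, and the documents do not support them.

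- *No estimate or interval is planned.* SAP 6.3.1 promises both for all secondary outcomes. What is missing is the adjustment, the effect measure and the interval method.
- *Ignoring the strata makes the test materially conservative.* True in principle, but with four centres and balanced blocks the simulation shows no appreciable effect on chi-square, and stratifying by centre alone would gain almost nothing. Fisher's test was not simulated.
- *Baseline is ignored for both outcomes.* Responder status is a reduction from baseline, so baseline is already part of that endpoint. The argument is stronger for acute-medication use.
- *The plan throws away 17 to 43 women.* That is 172 × 0.10 to 172 × 0.25, and it rests on an R² of 10 to 25% that appears nowhere in the documents. The weak-covariate scenarios fall below that range.

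A further fair point: if almost every woman used acute medication at baseline, a yes/no covariate would carry little information, and a logistic model could be unstable in sparse centres. The fix has to allow for both.

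**Conclusion.** The point holds as a matter of precision and consistency for two secondary outcomes. The planned tests are valid and the primary analysis is unaffected. Centre alone is worth essentially nothing in variance. Baseline is worth about 4 to 6% if weakly prognostic and up to about 27% if strongly so, which takes a half-width of 14.9 points to between 14.6 and 12.8.

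These sizes rest on assumed event rates, centre effects and covariate strengths, and the upper figure also assumes large centre differences. It is reasonable to expect earlier acute-medication use to predict later use, but the documents do not show how strongly. The change is worth making because it is nearly free; the trial's conclusions do not depend on it.

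**What to change.** In SAP 6.3.4, for both outcomes and for both cycles 1-3 and cycles 4-6, specify logistic regression with treatment, centre and the relevant baseline value:

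- **Responder rate:** baseline migraine days.
- **Acute-medication use:** baseline acute-medication use, preferably as an amount such as days of use if nearly all women are users. The diary supports this.

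Report a standardised (marginal) risk difference with a 95% CI, and name the interval method (delta method or bootstrap). Keep the chi-square or Fisher test as a supportive analysis, and as the stated fallback if the model does not converge because of sparse data. Missing-data handling need not change for this point.

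The cost is a paragraph in the SAP before database lock and code breaking, plus a little standard SAS code. No new data, visits or patients are needed. The small downside is one extra model and a fallback rule.

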#### **6.3.5 Safety Analyses**

##### **Adverse events**

All adverse events and serious adverse events will be listed. Adverse events include the acupuncture-related adverse events and medication-related adverse events. Chi-square test or Fisher's exact test will be used to compare the incidence of adverse events between the acupuncture group and medication groups.

##### **Participant's compliance**

The number and percentage of subjects who received at least 80% of the planned acupuncture treatment or medication will be analyzed with Chi-square test or Fisher's exact test.

## Blinding assessment

The number and percentage of participants who guess ‘true acupuncture plus placebo naproxen’ when asked if they received true acupuncture plus placebo naproxen or sham acupuncture plus naproxen treatment will be summarized by treatment, and Kappa analysis will be used to determine whether participants correctly guess their group assignment at a higher rate than would be expected by chance.

## 6.4 Update on the statistical analysis plan

As compared to the initial statistical analysis plan (SAP) published in Trials (Zhang XZ, Zhang L, Guo J, et al. Acupuncture as prophylaxis for menstrual-related migraine: study protocol for a multicenter randomized controlled trial. Trials. 2013;14:374), The original Analysis Plan has been amended as follows:

**Table 1. Major update of the statistical analysis plan**

| No. | Item                     | Published version                                                                                                                                                                                                                                                                                                                                                                 | Final version                                                                                                                            |
|-----|--------------------------|-----------------------------------------------------------------------------------------------------------------------------------------------------------------------------------------------------------------------------------------------------------------------------------------------------------------------------------------------------------------------------------|------------------------------------------------------------------------------------------------------------------------------------------|
| 1   | Primary outcome analysis | Analysis of variance (ANOVA) for repeated measures is used to compare the two groups. Comparisons within groups for the outcomes in each one of the time point are done using the Tukey’s post hoc test of Multivariate Analysis of Variance (MANOVA). Meanwhile, stratified analysis within four different centers will be performed to control confounding factor if necessary. | Mixed-effect model for primary analysis using baseline value as a covariate, treatment as a fixed effect, and center as a random effect. |
| 2   |                          |                                                                                                                                                                                                                                                                                                                                                                                   | More details were provided for the sensitivity analyses of primary outcome in primary analysis (see 6.3.3).                              |
| 3   | Analysis Software        | Every analysis is conducted by using the SPSS software version 13.0.                                                                                                                                                                                                                                                                                                              | For all statistical analyses, SAS 9.4 software will be used.                                                                             |

